### Sample size

Sample size has been calculated to estimate a proportions difference in the degree of adherence to the treatment of 20% between the exposed group (drug changes at the pharmacy) and the non-exposed group. It is estimated that adherence to treatments in the population undergoing chronic treatment is 50%, and the odds ratio (OR) of suffering an event of adherence decrease is double in the group exposed to drug changes (OR = 2) versus the non-exposed one.

For an alpha error of 0.05 and a beta error of 0.20, 237 patients would be necessary. Taking into account the effect of the doctor on adherence of their patients to treatment, it is considered that the outcome of each patient is not independent from other patients from the same cluster, so it is necessary to adjust the sample size because of the design effect. Considering that the number of included patients per doctor is 15, and assuming an intraclass correlation coefficient of 0.01 [17], the required sample size would be 240. If we estimate a 7% loss of patients to follow-up within a one-year period, the final sample size will be 259 patients.

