### Data analysis

Data will be reviewed prior to analysis to guarantee its quality. A descriptive analysis will be performed on the characteristics (age and sex) of patients who refuse to participate in the study and the reasons for it will be described.

A descriptive analysis of each of the variables will be carried out. The mean and typical deviation will be calculated in the case of symmetric distributions, and median and interquartile ranges will be estimated if the distribution is asymmetric. For categorical data, the frequency and percentage distributions will be shown. The difference of proportions will be estimated with its relevant confidence interval of 95%.

The association of each of the independent variables with the dependent variable (adherence decrease and medication errors) will be studied, using Pearson’s Chi-square test or Fisher’s exact test (when the conditions to apply Chi-square are not satisfied) as the statistical tools to compare proportions, and the Student’s T distribution or the Mann–Whitney U non-parametric test to compare the means.

A multivariate test with a logistic regression model will be performed, using the final combined variable (adherence and medication errors) as the dependent variable, and using as independent variables those identified to be associated in the bivariate analysis. All the hypothesis testing will be performed for all analysis’, and a p < 0.05 will be accepted as significant. All the analysis methods will be adjusted considering cluster randomizations [20]. Statistical data analysis will be performed using SPSS 18.0 software.

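### The sample-size paragraph names two design effects that cannot both hold (20 points and OR = 2), and 237 patients do not give 80% two-sided power for OR = 2.

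*Protocol article*

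**What the plan says.** All the design inputs are in the Sample size section of the protocol article. The target is first given as "a proportions difference in the degree of adherence to the treatment of 20% between the exposed group" and the non-exposed group. The next sentence puts adherence under chronic treatment at 50% and says that the odds ratio for an adherence decrease "is double in the group exposed to drug changes (OR = 2) versus the non-exposed one". The result follows: "For an alpha error of 0.05 and a beta error of 0.20, 237 patients would be necessary". The section does not give the sidedness of the test, any continuity correction, or the expected ratio of exposed to non-exposed patients.

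The same section then takes 15 patients per doctor and continues: "assuming an intraclass correlation coefficient of 0.01 [17], the required sample size would be 240". A 7% loss brings this to 259.

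The Data analysis section compares proportions "using Pearson’s Chi-square test or Fisher’s exact test", reports differences of proportions with 95% confidence intervals, fits a logistic regression to the combined outcome, and states that "a p < 0.05 will be accepted as significant". It mentions no one-sided test.

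**The concern.** A sample-size statement should let the reader see which effect the study can detect and with what probability. Here two effects are given as if they were the same, and the sample sizes they need differ by almost half. The odds ratio is the effect measure of the planned logistic regression, so a reader will naturally take the 80% to apply to OR = 2. If it does not, a null result on a patient-safety question would be read as firmer evidence than it is.

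**Working it through.** **Inputs.** From Sample size: 50% reference rate, OR = 2, 20-point difference, alpha 0.05, power 0.80, ICC 0.01, 15 patients per doctor, 7% loss, 259 patients. From Sampling: 30 doctors. From Data analysis: chi-square or Fisher tests, p < 0.05, 95% intervals, read here as two-sided. Equal groups are my assumption unless another ratio is named.

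**1. Are the two effects the same?**
- OR = 2 from 50%: odds 1 become 2, so p = 2/3 = 66.7%, a difference of 16.7 points. In the other direction it is 33.3%, the same distance.
- 20 points from 50%: (0.70/0.30)/(0.50/0.50) = 2.33. For 40% vs 60%, the OR is 2.25.
- The largest difference OR = 2 can give at any baseline is (√2 − 1)/(√2 + 1) = 0.172, at 41.4% vs 58.6%. So 20 points cannot be reached.
- Reading 20% as relative (50% vs 60%) gives (0.6/0.4)/1 = 1.5, which is not 2 either.

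**2. Formula.** With n₁ and n₂ = k·n₁, d = |p₁ − p₂| and p̄ = (p₁ + k·p₂)/(1 + k):

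n₁ = [z_α √((1 + 1/k) p̄(1 − p̄)) + 0.8416 √(p₁(1 − p₁) + p₂(1 − p₂)/k)]² / d²

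Here z_α is 1.960 two-sided or 1.645 one-sided. The continuity-corrected size at k = 1 is (n/4)[1 + √(1 + 4/(n·d))]².

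**3. Trying to reproduce 237.** For OR = 2, one-sided, k = 1: (1.645 × 0.6972 + 0.8416 × 0.6872)² / 0.1667² = 107.1 per group. With continuity correction, (107.1/4)(1 + √1.224)² = 118.8 per group, **237.7 in total**. This is the closest equal-group match found.

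**4. Two-sided sizes at 1:1.**
- OR = 2 (50% vs 66.7%): (1.960 × 0.6972 + 0.8416 × 0.6872)² / 0.1667² = 136.2 per group, 272.3 in total, or 274 as two whole groups. With continuity correction: 296.
- 50% vs 70%: (1.960 × 0.6928 + 0.8416 × 0.6782)² / 0.20² = 93.0 per group, 186 in total. Corrected: 206.
- 40% vs 60%: 194. Corrected: 214.

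The stated 237 lies between the two effects and matches neither.

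**5. Unequal groups, two-sided.**
- 40% vs 60% at 2.5:1, uncorrected: 67.5 + 168.7 = 236.2, which rounds up by group to 68 + 169 = **237**.
- 50% vs 70% at 2:1, corrected: 228 to 233, depending on which group is larger.
- OR = 2 at 2:1, uncorrected: 303 to 308. Imbalance moves OR = 2 further from 237.

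**6. Two-sided power for OR = 2.** At 1:1 with n per group:

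Power = Φ{[d − 1.960 √(2p̄(1 − p̄)/n)] / √([p₁(1 − p₁) + p₂(1 − p₂)]/n)}

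- 237 patients (n = 118.5): Φ{(0.1667 − 0.1255)/0.0631} = Φ(0.65) = **74%**. At 2:1, about 70%.
- All 259, no loss and no clustering: 78%.
- 259 × 0.93 = 241 analysed, before clustering: 75%.
- Design effect with 15 per doctor: 1 + 14 × 0.01 = 1.14; 241/1.14 = 211; power 69%.
- Design effect with 259/30 = 8.6 per doctor: 1 + 7.6 × 0.01 = 1.076; 241/1.076 = 224; power 72%.
- OR detectable with 80% power at 1:1: 2.21 at an effective 211 and 2.16 at 224, so about 2.2.

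**7. Two-sided power for 50% vs 70% at 1:1.** 89% at 237, and about 85% at an effective 211.

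**The case against.** The best defence is that 237 is not shown to be a miscalculation. Exposure is whatever the pharmacies dispense, the Discussion says it cannot be randomised, and no 1:1 split is claimed. With 40 to 47 presentations per drug (Background), unequal groups are plausible, and at 2.5:1 a two-sided calculation for 40% vs 60% gives 237. Alternatively, the Aim is worded directionally, and a one-sided calculation for OR = 2 lands on 237.7. Sidedness and ratio are also details that an article may leave to the full protocol. Finally, the section names the difference in proportions first, and for 20 points the power is ample at 1:1.

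Much of this stands. A reader might infer that 237 is an arithmetic error, that the authors used a one-sided test, or that the study is underpowered outright. The documents support none of these. There are at least two routes to 237, neither is declared, and the shortfall applies only if OR = 2 is the design effect. It would also be wrong to repair the paragraph by declaring equal groups, because nothing in the article supports that.

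Two things do not yield. The incompatibility of 20 points and OR = 2 needs no assumption about sidedness, ratio or software. And no ratio rescues OR = 2 two-sided: equal groups are close to the most favourable case, and 237 still falls short there. The one-sided route would contradict the usual two-sided reading of the chi-square tests and 95% intervals in Data analysis.

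**Conclusion.** The point holds in two parts. First, the article states two design effects that cannot both be true at any baseline. Second, if OR = 2 is the target, 237 patients do not give the stated 80% power with a two-sided 0.05 test at any exposure split. Power is about 74% at 1:1 and 70% at 2:1, and about 273 to 296 patients are needed at 1:1.

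The second part rests on reading the planned tests as two-sided and on a 50% reference rate. If 50% is the overall rate instead, the uncorrected two-sided requirement is still about 264. The 69–72% figures also use the article's own ICC and assume equal groups, so they are best-case values. Which calculation produced 237 cannot be settled from the article.

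**What to change.** In Sample size, name one effect with the pair of proportions it implies, and correct or delete the other. State the sidedness and the assumed exposed to non-exposed ratio that produced 237.

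- **If OR = 2 is kept:** replace the 80% claim with the two-sided power of the planned sample. At 1:1 this is at best about 75% with 241 analysed before clustering and about 69–72% after the stated ICC; it is lower if exposure is unbalanced. Alternatively, state the detectable OR, about 2.2 at 1:1.
- **If 20 points is kept:** delete OR = 2 and say that power for OR = 2 is below 80%.

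The cost is rewording one paragraph and stating a less favourable power. No extra patients and no change to the design or analysis are needed.

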**Methods/Design:**

We propose a multicentric observational longitudinal cohort study with a one-year follow-up period in 8 primary health care centers (PHCC) in the Community of Madrid. 259 patients who are ≥65 years old, hypertensive and/or dyslipidemic, undergoing treatment with enalapril and/or amlodipine and/or simvastatin, and under formal follow-up of chronic patients in primary health care will be selected by simple random sampling. The main outcome variable will be a final combined variable (adherence and medication usage errors). Other included variables will be: sociodemographic and clinical variables of the patient, degree of disease control, drug taken, number of changes in the appearance of each drug by the pharmacy, and the type and frequency of both avoidable and non-avoidable adverse effects during the follow-up period. A descriptive and a multivariate analysis of the variables will be carried out by means of a logistic regression model, using the final combined variable as the dependent variable (error and/or inadequate usage of the drug), and variables shown to be related to it during the bivariate analysis as the independent variables.

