### Sampling

Random sampling will be performed out of the list of patients who fit the selection criteria (≥65 years old, HTN and/or dyslipidemia, and treated with any of the 3 studied drugs) from each of the 30 participating doctors. Randomization will be performed by an independent researcher using computer software to create the randomization sequence (Excel 2007).

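### The stated cluster size and ICC do not give the stated sample size: 237 patients, 15 per doctor and ICC 0.01 lead to 271, not 240

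*Protocol article*

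**What the plan says.** The Sample size section of the protocol article builds the target in three steps.

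- **Base size.** "For an alpha error of 0.05 and a beta error of 0.20, 237 patients would be necessary". The target is given both as "a proportions difference in the degree of adherence to the treatment of 20"% and as an odds ratio of 2, with adherence of 50% as the reference.
- **Clustering by doctor.** The section says that outcomes of one doctor's patients are not independent and that the size must be adjusted for the design effect. The cluster size is given first: "Considering that the number of included patients per doctor is 15". The correlation and the adjusted total come next: "assuming an intraclass correlation coefficient of 0.01 [17], the required sample size would be 240".
- **Loss to follow-up.** A 7% loss takes 240 to 259. The Abstract repeats this as the planned enrolment: "259 patients who are ≥65 years old, hypertensive and/or dyslipidemic".

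The Sampling section draws patients at random "from each of the 30 participating doctors". The Data analysis section says that all analyses will be adjusted for clustering.

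**The concern.** An increase from 237 to 240 is only 1.3%. That is far too small for clusters of 15 at an ICC of 0.01, where the usual inflation is 14%. The inputs and the result stand next to each other and disagree, so this is not a matter of detail left out of a condensed article.

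The cluster size is also at odds with the rest of the plan: 15 patients from each of 30 doctors would be 450 patients, not 259.

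The 259 is the headline enrolment figure and carries the planned 80% power. If the printed ICC is right, the planning gives too little weight to a source of imprecision that the section itself calls necessary to allow for. A null result on changes in drug appearance could then be read as better powered than the stated assumptions support.

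**Working it through.** **Inputs, all from Sample size unless noted.** Base 237; alpha 0.05; power 80%; 15 patients per doctor (m); ICC 0.01; loss 7%; 30 doctors (Sampling).

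**1. The plan's own chain.**
- Loss step: 240/0.93 = 258.1, so 259. This step is correct.
- Implied design effect: 240/237 = 1.0127.

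**2. Design effect from the stated inputs.** DE = 1 + (m − 1) × ICC.
- DE = 1 + 14 × 0.01 = 1.14.
- 237 × 1.14 = 270.2, so 271.
- 271/0.93 = 291.4, so 292.

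**3. Design effect with the cluster size that 30 doctors imply.**
- 259/30 = 8.63; DE = 1 + 7.63 × 0.01 = 1.076.
- 237 × 1.076 = 255.1, so 255–256.
- 255.1/0.93 = 274.3 and 256/0.93 = 275.3, so about 275.
- Conversely, 259/15 = 17.3 doctors, not 30.

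**4. What would give 240.**

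| Explanation | Calculation | Result |
|---|---|---|
| Factor (m − 1) left out | 237 × 1.01 | 239.4 |
| ICC of 0.001, m = 15 | 237 × 1.014 | 240.3 |
| ICC of 0.01, smaller clusters | 1 + 0.0127/0.01 | m about 2.3 |

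The first two fit about equally well. The third matches nothing in the document.

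**5. Power with 259 enrolled, if 237 independent patients give 80%.** Evaluable: 259 × 0.93 = 240.9. Power = Φ(2.80 × √(n_eff/237) − 1.96).
- DE 1.14: n_eff = 240.9/1.14 = 211; power about 75%.
- DE 1.076: n_eff = 240.9/1.076 = 224; power about 78%.
- ICC 0.001 with m = 15 (DE 1.014): n_eff = 237.5; power about 80%.

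**6. Does 237 itself reproduce?** Two proportions, 1:1, two-sided 0.05, 80% power, no continuity correction:
- 50% vs 30% (20 points): 93 per group, 186 in total.
- Odds ratio 2 from 50%: odds of 1 become 0.5, so 33.3%, a difference of 16.7 points and not 20. This needs 137 per group, 274 in total.

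A figure near 237 appears only under conditions that the article does not state. With a continuity correction and 2:1 groups, 20 points needs 231 to 234. A one-sided test of odds ratio 2 with the correction needs 238.

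With 240 evaluable patients and DE 1.14 (about 105 effective per group at 1:1), power is about 85% for the 20-point difference and about 69% for odds ratio 2.

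**The case against.** A reader might infer that 259 patients cannot deliver 80% power. Three arguments stand against that.

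- **The base is uncertain.** The 75% and 78% hold only if 237 is the true 80% size. It does not follow from either stated effect at 1:1 two-sided. For the 20-point difference, power would still be about 85% at a design effect of 1.14; for odds ratio 2 it would be about 69%. The document does not fix which applies.
- **The wrong figure may be the ICC.** With 0.001 and 15 per doctor, 240 and 259 stand and only the printed ICC needs correcting. A reader might also infer that the (m − 1) factor was forgotten. That fits, but no better, and the source cited for the ICC is not available here.
- **1.14 is an upper bound.** The formula suits an exposure shared by the whole cluster. Here the exposure is a change made at the pharmacy, which differs between patients of one doctor, so the inflation is smaller. With DE = 1 + (m − 1) × ICC × exposure ICC, a value of 1.0127 would need an exposure ICC of 0.0127/0.14, about 0.09. The article states no such figure and invokes no such reduction.

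The error also affects planned precision only. The analyses are to be adjusted for clustering, so neither the estimate nor its interval is distorted by it.

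All of this limits the claim about power. None of it reconciles 237, 15 and 0.01 with 240, and nothing elsewhere in the document does so.

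**Conclusion.** The point holds as an inconsistency between stated inputs and stated result. As printed, they lead to 271 before loss and about 292 after, against 240 and 259. With the 8.6 patients per doctor that 30 doctors imply, they lead to 255–256 and about 275. Neither cluster size that the document supports gives 240 at an ICC of 0.01.

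If the ICC is 0.01, the cost in power is modest: about 5 points at 15 per doctor or about 2 points at 8.6. This takes 237 as the 80% size and the conventional design effect as the upper end. If the ICC is 0.001, there is no shortfall at this step and the error is in the printed ICC. The document does not support the categorical conclusion that the study is underpowered.

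**What to change.** 1. Check the ICC against its cited source.
2. Use one cluster size consistent with the 30 doctors (8 to 9 patients each for 259), or state a different number of doctors if it is to be 15 each.
3. State the single effect size, the ratio of exposed to non-exposed patients and the sidedness behind 237, and recompute it if it does not follow.
4. Then recompute the chain. If the ICC is 0.01, keep 259 and restate the power. On the present base that is about 75% at 15 per doctor or 78% at 8.6, but neither should be printed before step 3 is done. Any smaller inflation claimed because exposure varies within doctor should be stated with its assumed value. If the ICC is 0.001, correct the printed ICC.

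This rewords one paragraph and needs no extra patients. The only downside is that the stated power may become slightly less favourable.

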### Sampling

Random sampling will be performed out of the list of patients who fit the selection criteria (≥65 years old, HTN and/or dyslipidemia, and treated with any of the 3 studied drugs) from each of the 30 participating doctors. Randomization will be performed by an independent researcher using computer software to create the randomization sequence (Excel 2007).

### Variables

The main outcome variable is a final combined variable, defined as “having made some drug usage error and/or an inadequate adherence to treatment regimen”.

Error in drug usage is defined according to the classification proposed by Ruiz-Jarabo *et al*. [18]. The type of error will be recorded (wrong dose, wrong frequency), as well as if there was injury to the patient, in which case the type and severity will also be recorded.

Inadequate adherence will be considered if more than one forgotten dose is detected during the package counting and/or if any of the answers (Yes/No) to the 4 questions of the Morisky-Green test in its validated Spanish version [19] is wrong. In the case of discrepancies between the Morisky test and the counting, the outcome of the counting will prevail. Since one single forgotten dose is a very stringent level of accomplishment, if no adherence differences are observed, different degrees of adherence (80%, 90% and 110%) will be considered.

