Different studies have investigated the effects that changes in the appearance of drugs (package, shape, size, color) have on the control of chronic diseases. Of particular relevance is a systematic review by De Craen *et al*. [8], published in British Medical Journal, including 6 clinical trials that evaluated the effect of the color of pharmaceutical drug presentations on various factors, for example relating the drug color to a stimulating or depressive effect on the nervous system, or to the location of the effect. In addition to the placebo effect that different drug colors produce, color changes can confuse the patient, increasing the risk of errors. On the other hand, the change that happens at the pharmacies when dispensing medication with a different look may also affect the clinical control of the disease. The effects of drug appearance changes are centered on 2 mechanisms: medication errors (mistaking drugs, duplicating doses) and lack of adherence to treatment (either due to or independent of medication errors).

Undoubtedly, the most vulnerable population to these possible mistakes is the older, multi-medicated population. The changes in pharmaceutical presentations may mean an extra difficulty since they often suffer from visual deficiencies, and even cognitive ones, which can increase the risk of mistakes [9]. All this can generate confusion, forgetfulness, or duplication of dosages, which worsens adherence to the treatment, and therefore endangers their safety and even disease control [10]. The Spanish Ministry of Health, Social Services, and Equality itself establishes the investigation of the safety of medical treatments in the >65-year-old population as a strategic research line [11].

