## Methods/design

### Design

Observational longitudinal cohort study with a one-year follow-up period.

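### The count-based adherence rule is a fixed number of missed doses with no denominator or time window, so it can class many good takers as cases and is not tied to the 50% adherence used for planning

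*Protocol article*

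**What the plan says.** The primary outcome (Variables) is a composite: "having made some drug usage error and/or an inadequate adherence to treatment regimen". Its adherence component has two routes. The first is the package count: "Inadequate adherence will be considered if more than one forgotten dose is detected during the package counting". The second is the questionnaire: "if any of the answers (Yes/No) to the 4 questions of the Morisky-Green test in its validated Spanish version [19] is wrong". If the two disagree, the count decides: "In the case of discrepancies between the Morisky test and the counting, the outcome of the counting will prevail".

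The section does not say over what period missed doses are added up, or out of how many doses. It does not say whether they are pooled over drugs. The design is described as "Observational longitudinal cohort study with a one-year follow-up period", and Table 1 places package counting at months 3, 6, 9 and 12. Under Patients, eligibility requires at least one of three study drugs, so a patient may contribute one, two or three.

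The authors acknowledge that their threshold is a strict one and name percentage levels, but on a condition: "if no adherence differences are observed, different degrees of adherence (80%, 90% and 110%) will be considered". For planning, the Sample size section says: "It is estimated that adherence to treatments in the population undergoing chronic treatment is 50" (per cent). That sentence does not refer to the count rule. The Background gives a similar general figure for chronic treatments, also without reference to any count.

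**The concern.** An absolute count becomes harder to pass as more doses are observed. The same behaviour passes or fails according to the length of the counting period, the doses per day and the number of study drugs. Three things are at stake.

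- **Meaning of a case.** A patient who takes 98% or 99% of doses can be grouped with one who takes half.
- **Bias.** A patient on more drugs has more chances to miss two doses and also more chances of a presentation change at the pharmacy. The rule can therefore create an association between exposure and outcome that has nothing to do with appearance.
- **Power.** If far fewer than half of patients pass the rule, the planned sample was sized for a different outcome frequency.

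The rule is also one-sided. The Background names "medication errors (mistaking drugs, duplicating doses") as a mechanism of interest, but the count looks only for forgotten doses. If tablets are counted net, an extra dose cancels a missed one.

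**Working it through.** **Inputs from the article.** A case by count has two or more missed doses (Variables). Follow-up is one year with four counts (Design, Table 1). Patients take one to three drugs (Patients). Planning adherence is 50% and OR = 2; N is 240 after the clustering adjustment (Sample size).

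**Assumptions, because the documents give no miss rate.** One dose a day per drug, so n = 365 a year and about 91 per quarter; misses are independent with probability m.

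**The plan's own figure.** The 50% is a general estimate. It cannot be reproduced from the count rule, because no miss rate or window is given.

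**Step 1. Probability of being a case for a given taker.**
P(n, m) = 1 − (1−m)^n − n·m·(1−m)^(n−1)

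For m = 0.02, n = 365: 1 − 0.0006 − 0.0047 = 0.995.
For m = 0.01, n = 365: 1 − 0.0255 − 0.0941 = 0.880.
For m = 0.02, n = 91: 1 − 0.159 − 0.295 = 0.55; any of four counts: 1 − (1 − 0.5455)^4 = 0.96.
For m = 0.01, n = 91: 1 − 0.401 − 0.368 = 0.23; any of four counts: 1 − (1 − 0.231)^4 = 0.65.

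| Doses taken | One quarterly count | Any of four counts | Summed over the year |
|---|---|---|---|
| 95% | 0.95 | >0.999 | >0.999 |
| 98% | 0.55 | 0.96 | 0.995 |
| 99% | 0.23 | 0.65 | 0.88 |

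**Step 2. Dependence on number of drugs.** A 99% taker on two once-daily drugs, with misses pooled over 730 doses, is a case with probability 0.995. If instead either drug alone can trigger, and misses on the two are independent, it is 1 − (1 − 0.880)² = 0.986. With one drug it was 0.88. The behaviour per dose is unchanged.

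**Step 3. What 50% would require.** If all patients were alike, setting P = 0.5 gives m = 0.46% (99.5% taken) summed over the year, 0.78% (99.2%) for any of four counts, and about 1.8% (98.2%) at one count. The planning rate thus implies quite different behaviour under three readings that the text leaves open.

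**Step 4. Patients who differ.** Let the individual taking rate follow a beta distribution with mean 97%; a smaller total means wider spread.

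| Beta total | Cases, one count | Cases, any of four | Cases, year |
|---|---|---|---|
| 5 | 28% | 36% | 41% |
| 10 | 37.5% | 50.5% | 57% |
| 20 | 47.5% | 66% | 74% |
| 60 | 61% | 86% | 93% |
| 100 | 66% | 92% | 97% |

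Over the year, a mean of 95% gives 59% to 99.8% cases over the same spreads, and a mean of 99% gives 16% to 62%. The planned 50% lies inside the range for means of 97% and 99%, and below it for 95%.

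**Step 5. Consequence for power.** Take OR 2, two-sided alpha 0.05, 120 per group (240/2), no clustering, and the named rate in the non-exposed group:
z = [(p1−p2)√n − 1.96√(2p̄(1−p̄))] / √(p1(1−p1)+p2(1−p2)).
At 50% v 33.3%: (1.826 − 1.367)/0.687 = 0.668, so power is 0.75. At 20% v 11.1% adherent it is 0.48, and at 10% v 5.3% it is 0.28.

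**The case against.** The strongest reply is that the text does not state a one-year window. It speaks of what is found at package counting, and there are four separate counts. At a single count a 99% taker fails only 23% of the time. How visits are combined may be set out in the full protocol. This stands against any claim that the annual figures are the rule. It does not rescue the rule: the threshold is still an absolute number on every reading, and the any-of-four reading returns most of the way to the annual result.

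A reader might infer that nearly every good taker becomes a case and that an adherent half of the sample cannot exist. The documents do not support that. It needs a miss-rate distribution they do not give, and with wide between-patient spread 43% to 59% still pass over the year at a mean of 97% (beta totals 10 and 5).

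A reader might also infer that duplicated doses go unseen. That is too strong as well. The composite includes usage errors, with wrong dose and wrong frequency among the recorded types, collected at visits 2 to 5. A duplication detected there makes the patient a case. What remains is that the count itself, which overrides the questionnaire, cannot show one, and that only some duplications may be caught by the error component.

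Finally, the authors recognise that their level is strict and list percentages. That is to their credit, but the percentages come into play only after no difference has been seen, so they do not repair the primary definition.

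**Conclusion.** The concern holds in limited form. The count component of the primary outcome has no denominator, window or scaling. Under once-daily dosing with independent misses, it classes a 98% taker as a case with probability between 0.55 and 0.995, and a 99% taker between 0.23 and 0.88, depending on a reading the text does not settle. Case status rises with the number of study drugs, which also gives more chances of exposure.

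The 50% planning rate is not tied to the rule. At a mean of 97% taken, the annual case share may be anywhere from about 41% to 97%. A ceiling with loss of power is a real risk, not a demonstrated outcome. All these figures rest on assumed miss rates and spreads. That the outcome frequency depends so heavily on unstated choices is itself a reason to fix the definition. The change is worth making because it is cheap; the point does not invalidate the study.

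**What to change.** Before any outcome data are seen:

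1. Define primary count-based adherence as doses taken divided by doses prescribed, per drug and per interval between counts.
2. Fix one lower and one upper limit from the levels the protocol already lists. A band of 80% to 110% is one example. The article does not present these levels as a two-sided range, so the investigators should justify the choice.
3. State how drugs and visits combine into one patient-level outcome, and base the expected adherence rate in the sample size section on that definition.
4. Report the present count rule and the other listed levels as sensitivity analyses whatever the primary result shows.
5. Record surplus and deficit separately, so that an extra dose does not cancel a missed one.

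The cost is mainly protocol wording, since package counts are already scheduled at four visits; item 5 may need an extra field in the electronic notebook. The downside is that the strict definition becomes secondary.
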